## Abstract

**Background:**

Postoperative ileus (POI) is a well-known complication of abdominal surgery and is considered to be caused by a local inflammation in the gut. Previously it has been shown that both local and systemic inflammation can be reduced by stimulation of the autonomic nervous system via lipid rich nutrition. Stimulation of the autonomic nervous system releases acetylcholine from efferent vagal nerve endings that binds to nicotinic receptors located on the inflammatory cells leading to a decrease of pro-inflammatory mediators. Besides administration of nutrition there are other ways of stimulating the autonomic nervous system such as gum chewing.

**Methods/design:**

This prospective, placebo-controlled randomized trial will include 120 patients undergoing colorectal surgery which are randomized for gum chewing preoperatively and in the direct postoperative phase or a placebo. Postoperative ileus will be assessed both clinically by time to first flatus and time to first defecation and by determination of gastric motility using ultrasound to measure dimensions of the antrum. Furthermore the inflammatory response is quantified by analyzing pro-inflammatory mediators. Finally, markers of gut barrier integrity will be measured as well as occurrence of postoperative complications.

**Discussion:**

We hypothesize that chewing gum preoperatively and in the direct postoperative phase in patients undergoing colorectal surgery dampens local and systematic inflammation, via activation of the autonomic nervous system. Down-regulation of the inflammatory cascade via stimulation of the vagus nerve will ameleriote POI and enhance postoperative recovery.

**Trial registration:**

NTR2867

## Background

All intra-abdominal surgical procedures, even minimally invasive, are followed by a transient episode of gastrointestinal hypomotility making postoperative ileus (POI) a common clinical phenomenon after abdominal surgery. Therefore it has been suggested to accept POI as an obligatory physiological response of the intestine when performing abdominal surgery [1]. However, POI clearly has a significant impact on patient morbidity and results in a prolonged hospital stay and significantly contributes to annual healthcare costs [1]. Implementation of fast-track colorectal surgical programs have already shown promising results in reducing overall hospital stay by epidural analgesia, earlier nutrition, and mobilization after surgery [2]. Further reduction of this postoperative transient episode of gastrointestinal hypomotility will add to the enhanced recovery after colorectal surgery.

Research has shown that the extent of POI is influenced by the degree of surgical trauma, bowel manipulation and duration of surgery [3]. The inflammatory response is regarded to play a key role in the etiology of POI next to factors as sympathetic neural reflexes and release of hormones and neurotransmitters. It is thought that handling of the intestine during abdominal surgery triggers the inflammatory cascade leading to local inflammation in the intestinal muscular layer and influx of leucocytes [4]. This local inflammation is important in the development of gastrointestinal hypomotility after abdominal surgery and thus POI [1,4,5].

Previous studies have shown that vagus nerve stimulation ameliorates the local and systemic inflammatory response by binding of acetylcholine to α7 nicotinic ACh receptors (nAChrR) expressed on macrophages resulting in down-regulation of tissue macrophage reactivity and cytokine release [6,7]. This neural feedback loop can be triggered mechanically, pharmacologically, or in a physiological way via administration of enteral nutrition leading to an instant reduction of the inflammatory cascade. In experimental rat models we have previously demonstrated that preoperative administration of lipid-enriched enteral nutrition strongly attenuates the inflammatory response and reduces POI via release of cholecystokinin and activation of afferent vagal fibers [8,9]. However, clinical research is necessary to substantiate these effects in humans.

Activation of the autonomic nervous system can also be established by sham-feeding such as chewing gum [10-12]. Several studies have shown favorable effects of chewing gum after surgery for POI, measured as time to flatus and overall hospital stay [13-15]. However, the underlying mechanism remains unclear. Furthermore, based on experimental data previously referred to, chewing gum before the surgery would be expected to be most effective whereas. However, until now all studies administered chewing gum in the postoperative phase only.

In this study we investigate the effect of perioperative gum chewing on postoperative inflammatory mediators and evaluate clinical parameters such as POI in patients undergoing colorectal surgery.

### Study objectives

The primary objective of this study is to determine the effects of gum chewing in the perioperative phase on the extent of POI, overall hospital stay, and morbidity and mortality. The secondary objective is to determine the effects of gum chewing in the perioperative phase on postoperative inflammation and tissue damage.

### Methods and design

This trial is designed as a prospective placebo-controlled randomized trial in which the effect of chewing gum before and directly after colorectal surgery is compared to a placebo.

### Study population

Patients older than 18 years of age undergoing elective colorectal surgery are eligible for inclusion. In total 120 patients will be included. Patients are excluded in case of peritoneal carcinomatosis, inflammatory bowel disease, previous gastric or esophageal surgery (due to vagus nerve injury), a pre-existent ileostoma, allergy for mint, or gut motility influencing agents (for example, tricyclic antidepressants). Furthermore, patients with disturbance of the acetylcholine metabolism in any way, such as neurological diseases, medication (SSRI), or depression will be excluded.

### Participating centers

Patients eligible for enrolment will be included in two hospitals in the Netherlands; Orbis Medical Center in Sittard and Catharina Hospital Eindhoven.

### Randomization

After obtaining written informed consent patients will be randomly assigned to one of two groups by randomization software (TenAlea software adapted for minimization randomization). Based on this output a sequentially numbered, opaque, sealed envelope will be opened by which the allocation is revealed. Patients are either allocated to the experimental group and receive chewing-gum preoperatively and directly postoperative until start of enteral nutrition. The control group receives a placebo (dermal patch) for the same period, which does not contain any active ingredient, although patients are told otherwise. The dermal patch was chosen as placebo since mimicking the chewing of chewing gum in any other way would function as sham-feeding and thereby contaminate the results. The dermal patch can be considered comfortable, easy to use, and non-invasive, and serves the placebo purpose of patients assuming the patch to contain an active ingredient. Opening of the sealed envelopes and the administration of the intervention or the placebo is performed by nursing staff not participating in this trial. Ethical approval for this study was granted by the Medical Ethics Committee Atrium-Orbis-Zuyd (Heerlen, the Netherlands).

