### Statistical analysis

Sample size is calculated with a Power analysis and was aimed at POI and length of stay. We considered a decrease of 1 day of admission from the average 5 days for current fast-track protocols in our center to be clinically relevant. To achieve a power of 0.9 with an alpha of 0.05 and a beta of 0.1 for a decrease of 1 day of the mean length of stay each group needs to consist of 60 subjects when performing a unpaired *T*-test. The analysis will be done according to the intention-to-treat principle. When using POI as primary outcome parameter for the Power analysis slightly fewer patients would be required per group due to the larger effect size. With the current sample size, both parameters are adequately powered.

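### Patients are minimised in two hospitals, yet the only test named is an unadjusted t-test, which wastes precision if the minimisation factors or centre predict length of stay

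*Protocol article*

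**What the plan says.** Three statements in the protocol article bear on this point.

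- **Randomization:** patients are assigned by "randomization software (TenAlea software adapted for minimization randomization". The section lists no minimisation factor, gives no random element, and does not say whether centre is a factor.
- **Participating centers:** "Patients eligible for enrolment will be included in two hospitals in the Netherlands".
- **Statistical analysis:** "each group needs to consist of 60 subjects when performing a unpaired *T*-test". This is the only test named anywhere, and it stands in the sample-size calculation. The one sentence on the analysis itself reads "The analysis will be done according to the intention-to-treat principle". No adjusted model or centre term is mentioned, and none is excluded.

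The planning mean comes from one place: "We considered a decrease of 1 day of admission from the average 5 days for current fast-track protocols in our center".

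**The concern.** Minimisation makes the arms alike on chosen factors. If those factors predict stay, the treatment difference varies less from trial to trial than it would under simple randomisation. An unpaired t-test does not know this. It leaves the variance due to the factors in its error term, so its standard error describes a design that was not used.

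The stakes are efficiency and calibration, not false positives: a test below its nominal 5% level, intervals wider than needed, and some power given up. Centre raises a related issue, because two hospitals recruit while the planning mean refers to one centre. If centre is a minimisation factor, the same argument applies to it. If it is not, the t-test keeps its nominal level with respect to centre, but any centre difference in stay still adds avoidable noise.

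**Working it through.** **Inputs from the article.** Total 120, 60 per group; difference 1 day from a mean of 5; alpha 0.05 (sidedness not stated); power 0.90. **Assumed, because the article gives no value:** R², the share of variance in stay that the factors explain, taken from 0 to 0.30.

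**Step 1: the plan's own figure.** The 60 per group cannot be reproduced, because no SD is given. Solving backwards, two-sided:

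SD = 1 / [√(2/60) × (1.960 + 1.282)] = 1 / (0.1826 × 3.242) = 1.69 days

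The exact t calculation gives 1.68, used below. A one-sided alpha would imply 1.87.

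**Step 2: level of the t-test under balance.** If the arms are balanced on the factors, the unadjusted statistic has variance of about 1 − R² under the null, so

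type I error = 2 × [1 − Φ(1.96 / √(1 − R²))]

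At R² = 0.20 this is 2 × [1 − Φ(1.96 / 0.894)] = 2 × [1 − Φ(2.19)] = 2.8%.

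**Step 3: interval width.** Adjustment reduces the SD to SD × √(1 − R²), so the unadjusted interval is wider by the factor 1 / √(1 − R²). At R² = 0.20 this is 1 / 0.894 = 1.118.

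**Step 4: simulation.** 4,000 trials per scenario, 120 patients, three assumed binary factors, minimisation with an assumed 0.8 biased coin, SD 1.68. The t-test was compared with a linear model containing the factors. The Monte Carlo standard error is about √(0.05 × 0.95 / 4000) = 0.003 for type I error and √(0.9 × 0.1 / 4000) = 0.005 for power.

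| R² (assumed) | Type I, formula | Type I, t-test | Type I, adjusted | Power, t-test | Power, adjusted | Unadjusted interval wider by |
|---|---|---|---|---|---|---|
| 0 | 5.0% | 0.050 | 0.049 | 0.906 | 0.906 | 0% |
| 0.05 | 4.4% | 0.048 | 0.053 | 0.913 | 0.921 | 3% |
| 0.10 | 3.9% | 0.043 | 0.055 | 0.911 | 0.930 | 5% |
| 0.20 | 2.8% | 0.026 | 0.043 | 0.920 | 0.947 | 12% |
| 0.30 | 1.9% | 0.021 | 0.053 | 0.934 | 0.974 | 20% |

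Coverage of the unadjusted 95% interval was 0.948, 0.958, 0.963, 0.968 and 0.979 down the table.

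**Step 5: sensitivity to the set-up.** A second simulation (two binary factors, 0.9 coin, 3,000 trials) gave t-test type I errors of 3.8%, 2.5% and 2.2% at R² 0.10, 0.20 and 0.30. Power was 0.913, 0.922 and 0.929 unadjusted against 0.931, 0.952 and 0.968 adjusted. The conclusion does not depend on the number of factors or the coin.

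**The case against.** The strongest objection is that the t-test is only a sizing device. Trials are often sized on a simple test and analysed with covariates. The full protocol and the analysis plan are not shown, and either may list the factors and adjust for them. This stands, and it limits the point: a reader might infer that the sponsor has decided on an analysis that ignores the minimisation factors and centre, but the article fixes no model and excludes no covariate. What remains is that the one comparison it names, if followed as written, does not match the allocation it states.

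Three further inferences are tempting and not supported.

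- **That the trial loses its planned power.** It does not. At an SD of about 1.68 the t-test keeps 0.90 or slightly more at every R² examined. The loss is only relative to an adjusted analysis.
- **That intervals are certainly too wide.** This needs prognostic factors. At R² = 0 there is no effect, and at 0.05 it is about 1 power point and 3% in width. Nothing in the article says where R² lies.
- **That the two hospitals discharge patients differently.** The article gives no evidence of this. Its Study outline section describes a common fast-track protocol for both arms and known fast-track discharge criteria. A centre difference is possible but not documented.

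**Conclusion.** The point holds in a conditional form. The stated allocation is minimisation in two hospitals, and the only named comparison is unadjusted. If the factors predict stay, that comparison is conservative and less precise than one that adjusts for them. The direction is secure, since the formula and both simulations agree.

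The size is not known. Over the assumed R² range of 0 to 0.30 it runs from nothing to about 4 points of power and a 20% wider interval, with type I error falling to about 2%. These power figures rest on a back-solved two-sided SD of 1.68 days, a linear effect of the factors, and normally distributed stay. Validity is not threatened: the error is on the cautious side. This is a worthwhile improvement rather than a serious defect.

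**What to change.** State the minimisation factors and whether centre is one of them. Make the primary length-of-stay comparison a linear model for mean stay with terms for treatment, every factor used in the minimisation, and centre. Report the adjusted difference in days with its 95% interval, and keep the unpaired t-test as a supportive analysis. If the analysis plan already does this, one clarifying sentence is enough.

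A linear model for mean stay is preferable here to log stay, a Cox model or a van Elteren test, because those do not target the 1-day difference in means on which the trial is sized.

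The cost is small. The factors are already entered in the randomisation software, so no new data or patients are needed. With three binary factors, for example, residual degrees of freedom fall from 120 − 2 = 118 to 120 − 5 = 115, and by one more if centre is added separately. The article reports recruitment as ongoing, so the model can be fixed before the analysis. That also removes any later choice between adjusted and unadjusted results.

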### Study outline

All subjects are allowed to drink clear fluids up to 2 h before surgery. Patients allocated to the experimental group start chewing gum 3 h preoperatively until surgery, 3 h postoperatively gum chewing is continued. Though patients are free to chew the gum to their own liking during these periods, they are being encouraged to chew the gum as often as possible. Gum chewing is discontinued at the moment at which normal solid food intake is being tolerated. The control group will receive a dermal patch at the same moments as the experimental group and are instructed not to chew any gum pre- or postoperatively. The patch will be placed at a standardized location in the lumbar region. Both groups receive the same fast-track surgical protocol as any other patients undergoing colorectal surgery in our center. At moment of inclusion, consent is obtained and patient information will be given in which both the gum chewing as the placebo (dermal patch) are described as being possibly effective. The expected effective intervention (gum chewing) and definitive conclusion will not be revealed until completion of the trial.

Blood and urine samples will be collected at several predefined moments in relation to the incision time of the procedure. Tissue samples from the resected colorectal segment are collected during the surgical procedure for immunohistochemistry, Western blot, and polymerase chain reaction (PCR) analysis. When collected all samples are stored at −80 °C until further analysis. The inflammatory response is measured by analyzing the blood plasma and tissue samples for inflammatory mediators (amongst which TNF-alpha and interleukins such as IL-6 and IL-8). Intestinal tissue damage is measured by analysis of several markers for intestinal damage in blood and tissue samples such as intestinal fatty acid binding protein (I-FABP).

Patient characteristics and clinical parameters, such as vomiting and time to return of a normal gastrointestinal transit, are registered in an electronic database.

On admission, a quality of life checklist (EORTC QLQ C-30) for cancer patients is filled out, which is repeated at time of discharge. Patients are ready for discharge according to known criteria as in fast-track surgery [16,17]. At the second postoperative day gastrointestinal transit is assessed by ultrasonography by a standard protocol.

### Antrum measurements

POI is often measured clinically based on parameters such a time to first flatus and first defecation. These are more or less subjective parameters of gastric motility [14]. To provide an objective and precise parameter for gastric motility an ultrasound of the gastric antrum is performed in the evening of the second postoperative day. Previous studies have already shown antrum measurements to be representative for determining gastric emptying and thereby gastric motility [18-20]. In short, subjects receive a standardized meal after which antrum measurements are done. All results of these measurements are registered in an electronic database.

### Statistical analysis

Sample size is calculated with a Power analysis and was aimed at POI and length of stay. We considered a decrease of 1 day of admission from the average 5 days for current fast-track protocols in our center to be clinically relevant. To achieve a power of 0.9 with an alpha of 0.05 and a beta of 0.1 for a decrease of 1 day of the mean length of stay each group needs to consist of 60 subjects when performing a unpaired *T*-test. The analysis will be done according to the intention-to-treat principle. When using POI as primary outcome parameter for the Power analysis slightly fewer patients would be required per group due to the larger effect size. With the current sample size, both parameters are adequately powered.

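### The protocol fixes neither one primary outcome nor one POI variable, so control of error at 5% is not secured and the power claim for POI cannot be checked

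*Protocol article*

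**What the plan says.** - **Primary objective** (Study objectives): "effects of gum chewing in the perioperative phase on the extent of POI, overall hospital stay, and morbidity and mortality". The four items are not ranked.
- **What the trial is sized for** (Statistical analysis): "Sample size is calculated with a Power analysis and was aimed at POI and length of stay".
- **The calculation shown** (same section): "We considered a decrease of 1 day of admission from the average 5 days", then "To achieve a power of 0.9 with an alpha of 0.05 and a beta of 0.1", giving 60 per group for an unpaired t-test. This concerns length of stay only. No SD is stated.
- **POI in the same paragraph**: POI is considered as an alternative primary parameter that would need slightly fewer patients because its effect is larger. No effect size, SD or sample size is shown for it. The paragraph closes: "With the current sample size, both parameters are adequately powered".
- **How POI is measured** (abstract, Methods/design): "clinically by time to first flatus and time to first defecation and by determination of gastric motility using ultrasound". The Antrum measurements section describes the two clinical times as rather subjective and presents the ultrasound as the objective measure. It does not say which one carries the POI comparison.

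**The concern.** A sample size supports a confirmatory claim only when one variable, or an explicit rule over several, stands behind it. Here two outcomes share the primary role, and one of them could be any of three variables.

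Two things follow. The statement that POI is adequately powered cannot be checked, because no variable, effect or SD is attached to it. And since the deciding result is not fixed, it could be chosen once the data are known, which is the situation that a 5% error rate is meant to exclude. Morbidity and mortality in the primary objective add to the ambiguity, although no test or power is attached to them.

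**Working it through.** **Inputs.** From the Statistical analysis section: alpha 0.05 (given once, for stay; sidedness not stated), power 0.90, difference 1 day, 60 per group. From the abstract: three POI measures. Not in the article, hence assumptions: the SD of stay, the correlation between outcomes, and the power for POI.

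**1. The plan's own figure.** Without an SD, 60 per group cannot be reproduced, only inverted. From n = 2·SD²·(z_α + z_β)²/Δ²:

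- Two-sided: SD = √(60/2)/(1.960 + 1.282) = 5.477/3.242 ≈ 1.69 days (1.68 with the t distribution).
- One-sided: SD = 5.477/(1.645 + 1.282) ≈ 1.87 days.

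The two-sided value is used below.

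**2. Any one significant result counts, each tested at 0.05.** For k independent tests the chance of at least one false positive is 1 − 0.95^k:

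- k = 2: 1 − 0.9025 = 9.75%.
- k = 4: 1 − 0.8145 = 18.5%.

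For equally correlated normal test statistics, two-sided:

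| Tests | corr. 0 | 0.5 | 0.7 | 0.9 |
|---|---|---|---|---|
| Stay + one POI measure (2) | 9.75% | 9.1% | 8.4% | 7.0% |
| Stay + three POI measures (4) | 18.5% | 15.6% | 13.1% | 9.4% |

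**3. Stay and one fixed POI measure must both be significant.** The error rate is at or below 5%. Power is the probability that both succeed:

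- Each at 0.90 and independent: 0.90 × 0.90 = 0.81.
- Each at 0.90, correlation 0.5: 0.83.
- POI power assumed at 0.92-0.95, correlation 0.5-0.9: about 0.85-0.89.

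Joint power cannot exceed the 0.90 for stay, so it falls short of 0.90 throughout this range.

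**4. Alpha split equally between the two outcomes.** Power for stay at alpha 0.025 and 60 per group is Φ(3.242 − 2.241) = Φ(1.000) ≈ 84%. Keeping 90% would need n = 2 × 1.69² × (2.241 + 1.282)² ≈ 71 per group, or 142 in total against the planned 120. On the one-sided reading the split gives Φ(2.926 − 1.960) ≈ 83%, so the conclusion does not turn on sidedness.

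**5. One primary outcome, or a fixed order.** Stay is tested first at 0.05 with 60 per group. The stated alpha and the stated power for stay both stand unchanged.

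**The case against.** The strongest reply is that the article states no rule under which any single significant result makes the trial positive. It gives 0.05 once, inside the calculation for stay, and never presents it as an error rate for a family of tests. A decision rule or testing order may stand in an analysis plan that is not shown, and its absence from a condensed article is not a fault. All of this stands. A reader might infer that the 5% rate is definitely not delivered, and the documents do not support that.

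A reader might also infer an error rate of two to five times 5%. That does not hold either. The upper end needs six independent tests, with mortality counted as a full 5% test. With 60 per group, Fisher's exact test gives p = 0.057 for 5 versus 0 deaths. Its true size is about 0.001 at an assumed 2% mortality and about 0.011 at 5%, so mortality adds almost nothing. POI and stay are also unlikely to be independent, since the Discussion treats shorter stay as a consequence of less POI. At correlation 0.9, two tests give 7.0%, which is less than double.

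Finally, a joint power of 0.81-0.83 is pessimistic if POI is better powered than stay, as the text implies.

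What the reply does not reach is what the article itself sets down. It sizes the trial for two outcomes, shows a calculation for one, and declares both powered, with POI left as three candidate variables. A later alpha split would not fit the stated 90% power at 60 per group.

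**Conclusion.** The point holds in a limited form. The protocol fixes neither one primary outcome nor one POI variable, so control at 5% is not secured, and the power claim for POI rests on nothing that can be checked.

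The size depends on a rule that the article does not give. An any-one-wins rule costs error, a both-must-win rule costs joint power, and an alpha split costs power for stay. Of the routes examined, only a single primary outcome or a fixed order keeps both the 5% and the 90% for stay at 60 per group. The split-alpha figure rests on the back-solved SD, the error ranges on equally correlated normal tests, and the joint-power range on assumed POI power.

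Morbidity and mortality are a lesser matter of placement: they stand in the primary objective without a test or power. They should not be counted as further full-size tests.

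**What to change.** Before analysis (the Trial status section reports that recruitment is ongoing):

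1. Name length of stay as the single primary outcome, since 60 per group is derived from it.
2. Test one pre-named POI variable second, in fixed sequence at 0.05, only if stay is significant. The sponsor should choose it in light of the Antrum measurements section, which ranks the ultrasound above flatus and defecation for objectivity.
3. Make the remaining POI measures secondary, and move morbidity and mortality out of the primary objective to secondary or descriptive.
4. Delete the closing sentence on both parameters being powered, or replace it with the effect size, SD and power for the named POI variable.

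This changes wording only and needs no extra patients. The cost is that a POI result is no longer confirmatory when stay is not significant. The chance of reaching a confirmatory POI claim is then the joint power in step 3 of the working, which is below 0.90. If the sponsor regards POI as the central question, that cost should be weighed openly before the order is fixed.
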